Clinical pathways for stroke rehabilitation are inherently influenced by magnitude and heterogeneity of the initial deficits. Severe stroke patients are usually addressed to rehabilitation hospitals where standard programs are primarily devoted to motor, sensory and language deficits. Early cognitive assessment and cognitive rehabilitation are not routinely performed in the acute stroke setting, and there is a lack of an established pathway dedicated to post-stroke cognitive deficits (Suda et al., 2020). Mild stroke patients are frequently discharged at home, thus increasing the risk that persistent cognitive deficits are underdiagnosed and, ultimately, undertreated (Ishiwata et al., 2025). Data on the efficacy of cognitive rehabilitation in both scenarios are needed to identify the characteristics of stroke patients that could maximally benefit of such cognitive interventions. In 2011 a representative group of stroke survivors, carers, and health professionals convened a consensus meeting aimed at compiling the top 10 research priorities of life after stroke, and the most important unsolved question was: “What are the best ways to improve cognition after stroke?” (Pollock et al., 2012, 2014). In line with this, the NICE guidelines for stroke suggest the inclusion of cognitive rehabilitation within rehabilitation pathways, but concluded also that literature does not provide robust evidence about which interventions will be most effective. Despite its social and economic burden is increasingly recognized, cognitive impairment after stroke is still a neglected consequence compared to other neurological deficits for which rehabilitation pathways are generally more available.^1^

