	Discharge^°^	• Date of discharge • Discharge destination (home, home with outpatient neurorehabilitation pathway, neurorehabilitation hospital) • NIHSS
	Quality of life	• Stroke adapted sickness impact profile (SA-SIP)^*^ (Buck et al., 2000) • EuroQol scale^*^ (Dorman et al., 1998)
	Mood	• Center for Epidemiologic Studies Depression scale (CES-D)^*^ (Lau et al., 2023)

* Patient interview or evaluation.

° Clinical record.

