At baseline, patients undergo a cognitive and mood assessment to investigate: neglect (star cancellation test; Halligan and Robertson, 2000; Wilson et al., 1987), apraxia (ideomotor apraxia test; Spinnler and Tognoni, 1987), fragility [Tilburg Frailty Indicator—TFI (Gobbens and Uchmanowicz, 2021; Mulasso et al., 2016) and Fried criteria (Fried et al., 2001) with IPAQ (Mannocci et al., 2010)] and cognitive reserve (CRI Questionnaire; Nucci et al., 2012). At 7 days after discharge, a telephone interview is conducted to investigate: functional state (ADL, IADL, and mRS; Katz et al., 1963; Lawton and Brody, 1969), quality of life [Stroke adapted sickness impact profile—SA-SIP (Buck et al., 2000) and EuroQol (Dorman et al., 1998)] and mood (CES-D; Lau et al., 2023).

During hospitalization, the caregiver interview involves the investigation of the patient's premorbid functional state (ADL and IADL; Katz et al., 1963; Lawton and Brody, 1969) and the possible presence of cognitive decline before stroke (IQ-Code; Jorm, 2004; van Nieuwkerk et al., 2021).

Stratified block randomization is used to assign participants to the experimental (tele-rehabilitation) or control group (standard care). This method ensures an even distribution of participants across predefined strata and minimizes imbalance in group sizes over time. Participants are stratified based on age, sex, NIHSS and MoCA scores. These variables were selected due to their potential influence on the study outcomes. Blocks of fixed size were generated to ensure that the number of participants in each group remained balanced throughout the enrollment process.

Randomization sequences were created using a computer-based random allocation software by the researchers of the Institute of Neuroscience (Florence) of the Italian National Research Council, who were not involved in participant recruitment or data collection and were in charge of the centralized randomization procedure. To prevent selection bias, randomization sequences are concealed from field workers.

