### Statistical analysis

The sample size was determined a priori based on data reported in previous studies and reviews on cognitive rehabilitation, along with feasibility and logistical considerations. These included the actual flow of stroke patients admitted to Careggi University Hospital and the Intensive Rehabilitation Unit of IRCCS Don Gnocchi during the planned 12-month enrollment period, along with the availability of dedicated spaces, appropriate settings, and personnel.

Yearly, ~400 stroke patients are admitted to the Stroke Unit of Careggi University Hospital, and ~130 patients are referred to the Intensive Rehabilitation Unit of IRCCS Don Gnocchi. Based on an estimated screening pool of ~550 patients during an enrolment period of 12 months, and accounting for an expected frequency of cognitive deficits in 75% of stroke patients during acute phase (enrolment period), as well as a substantial proportion of ineligible patients and refusals, we estimate to enroll ~100 patients. Eligible patients will be randomized in a 1:1 ratio: 50 will be allocated to the experimental group receiving the telerehabilitation program and 50 to the control group receiving standard care. Both groups will be balanced for key demographic and clinical characteristics. This sample size was determined based on pilot studies and a power analysis to ensure a statistical power of 80% to detect significant differences between the two groups assuming a two-sided alpha level of 0.05.

The data management system will include automatized procedures of data analysis. Specifically, independent sample *t*-tests and chi square tests will be used to compare demographics, vascular risk factors, and global cognitive and functional status, and the results will be available in real time during the whole enrollment period. Stratified block randomization will be employed to balance potential prognostic factors—such as age, gender, MoCA scores, and NIHSS scores—across the two groups, minimizing confounding and enhancing internal validity.

At the conclusion of the 6-month follow-up, primary and secondary outcome analyses will be conducted using SPSS version 28. The analysis will focus on three main objectives:

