1) Effectiveness in Reducing Persistent Cognitive Impairment: The efficacy of the telerehabilitation program in reducing the incidence of persistent cognitive impairment at 6 months will be assessed using a chi-square test to compare proportions between groups.2) Impact on Daily Life Abilities: The effectiveness of the telerehabilitation program in improving patients' functional outcomes will be evaluated through within-group (pre-post) and between-group comparisons. Dependent variables will include functional independence measures, quality-of-life scores, changes in frailty status, and cognitive performance metrics.3) Predictors of Effectiveness of the telerehabilitation program: Multivariate regression models will be used to identify predictors of telerehabilitation efficacy. Covariates will include demographics (age, sex), cognitive resilience, baseline cognitive and functional abilities, TFI score, index stroke severity, and pre-existing brain structural changes.

The enrolment activities began in April 2024 and are ongoing. Since then, consecutive patients admitted with a diagnosis of ischemic or hemorrhagic stroke are being evaluated for participation in the study.

The flow-chart of the study is shown in Figure 2.

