Another limitation concerns the inclusion and exclusion criteria: usually, in stroke cases, severe strokes and patients with aphasia are excluded, which obviously limits the generalizability of the results. Based on the inclusion and exclusion criteria, we will be able to assess patients with severe cognitive deficits, including mild aphasia, as well as those with very mild deficits, embracing the whole spectrum of post stroke cognitive deficits. By means of the collaboration between a University Hospital Stroke Unit and a Neurorehabilitation ward in rehabilitation Hospital we aspire to test cognitive telerehabilitation in a wide spectrum of stroke severity, in both ischemic and haemorrhagic strokes. This approach will enable the inclusion of patients with a broad spectrum of post-stroke deficits.

A further limitation relates to the risk of non-adherence to treatment. The intensity of the intervention protocol (daily 1-h sessions for 8 weeks) may pose challenges to patient compliance and increase the likelihood of dropout. For this reason, the CIPSTER trial is designed as a feasibility study.

In addition, it is important to acknowledge that the observed improvements in cognitive functions at six-month follow-up might partially reflect the natural course of post-stroke recovery, which tends to be more pronounced in the first few months. Therefore, attributing all the cognitive gains only to the intervention may be confounded by this spontaneous recovery process. The longitudinal evaluation will allow this to be clarified. In fact, the study outcomes will be defined according to standardized criteria based on an extensive neuropsychological and functional evaluation. To limit dropout rates, we also plan to include those patients who will not be able to attend the final visit in person, allowing an extensive phone interview. Of course, at the end, we will compare possible differences between groups.

Last but not least, CIPSTER will shed light on the feasibility of managing cognitive problems also in a very acute phase after stroke, within 3 weeks from stroke onset. Compared with the available evidence, only few studies examined cognitive outcome in this acute phase (Zucchella et al., 2014; Prokopenko et al., 2013), with most focusing on the chronic phase (Ye et al., 2022).

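### Patients come from an acute stroke unit and a rehabilitation unit, but enrolling unit is absent from the strata, the primary comparison and the listed moderators

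*Protocol article*

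**What the plan says.** The Background of the protocol article describes two routes after stroke: "Severe stroke patients are usually addressed to rehabilitation hospitals", while "Mild stroke patients are frequently discharged at home". It continues: "Data on the efficacy of cognitive rehabilitation in both scenarios are needed to identify the characteristics of stroke patients". The Discussion carries both settings into this trial. Of the collaboration between the stroke unit and the neurorehabilitation ward it says "we aspire to test cognitive telerehabilitation in a wide spectrum of stroke severity, in both ischemic and haemorrhagic strokes". It also names finding the type of patient who benefits as a leading purpose of the trial.

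The design and analysis sections say the following.

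- **Strata** (Methods, randomisation paragraph): "Participants are stratified based on age, sex, NIHSS and MoCA scores".
- **Primary comparison** (Statistical analysis, objective 1): a chi-square test of two proportions, with no adjustment mentioned.
- **Predictors of efficacy** (Statistical analysis, objective 3): "Covariates will include demographics (age, sex), cognitive resilience, baseline cognitive and functional abilities, TFI score, index stroke severity, and pre-existing brain structural changes".
- **Control arm** (Methods): usual care as indicated by each patient's own physicians.
- **Recorded data** (Table 1, Discharge): "Discharge destination (home, home with outpatient neurorehabilitation pathway, neurorehabilitation hospital".
- **Patient flow** (Statistical analysis): about 400 stroke-unit admissions a year, and about "130 patients are referred to the Intensive Rehabilitation Unit of IRCCS Don Gnocchi".

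**The concern.** Background care in this trial can range from discharge home to inpatient neurorehabilitation. Enrolling unit probably predicts outcome, because severity influences both the route a patient takes and later cognition. Where such a factor is known before randomisation, leaving it out of the comparison gives up some precision. It also leaves any chance imbalance in the estimate.

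The second issue is interpretation. Objective 3 is the analysis meant to show who benefits. Its list omits the setting that the article itself uses to frame the need for evidence. As listed, no analysis would show whether the result looks alike in patients from the two units. If such an analysis were added after outcomes are known, it would be post hoc.

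**Working it through.** **Inputs.** The article gives no figure for imbalance by unit. Its 80% power claim cannot be reproduced, because it states no event rates or effect size. With 50 per arm and two-sided alpha 0.05, 80% power corresponds to, for example, 50% v 23% impaired.

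- N = 100 and 50 per arm: Statistical analysis.
- Rehabilitation-unit share: 130/(400 + 130) = 0.245, so about 25 of 100. This is an assumption: it treats the two flows as separate pools with equal enrolment yield, and the article states neither.
- Overall risk of impairment at 6 months: about 50%, borrowed from the medium-to-long-term figure in the Background (assumption).
- Risk gap between units: 20 to 40 points (assumption; the article gives no value).

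**Step 1: chance imbalance.** Without stratification by unit, the number of rehabilitation-unit patients in one arm is hypergeometric (N = 100, K = 25, n = 50).

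- Variance = 50 × 0.25 × 0.75 × (50/99) = 4.73, so SD = 2.18 patients. The 95% range is 8 to 17 of 50.
- SD of the between-arm difference in proportion = 2 × 2.18/50 = 0.087, about 9 points. At a 50% share it is about 10 points.
- A split of 16 v 9 (14 points) or worse has probability 0.165. An imbalance of 20 points or more has probability 0.02 at a 25% share and 0.07 at a 50% share.

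NIHSS and MoCA are strata and are probably related to unit, so the true SD is smaller. The article does not allow the reduction to be computed.

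**Step 2: effect on the risk difference.** Shift = imbalance × risk gap.

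| Imbalance | Gap 20 points | Gap 40 points |
|---|---|---|
| 8.7 points (1 SD) | 1.7 | 3.5 |
| 10 points | 2.0 | 4.0 |
| 14 points | 2.8 | 5.6 |

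**Step 3: comparison with sampling error.** SE of the risk difference = √(2 × 0.5 × 0.5/50) = 0.10. A one-SD imbalance therefore moves the estimate by 0.17 to 0.35 SE, and a 14-point imbalance by about 0.3 to 0.6 SE.

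**Step 4: what adjustment could gain.** Share of outcome variance explained by unit = 0.25 × 0.75 × gap²/(0.5 × 0.5). This is 0.03 for a 20-point gap and 0.12 for a 40-point gap.

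**Step 5: what a moderator analysis could show.** Take a 28-point effect (50% v 22%) in the rehabilitation unit and none in the other, with a two-sided 5% Wald test on the difference of risk differences.

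- 25% share (12 and 38 per arm): SE = √[(0.25 + 0.1716)/12 + 0.50/38] = 0.220, giving power of 25%.
- 50% share (25 and 25 per arm): SE = √[(0.25 + 0.1716)/25 + 0.50/25] = 0.192, giving power of 31%.

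Power to detect 50% v 22% within a unit is 29% with 12 per arm and 73% with 38 per arm.

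**The case against.** Four points can be made for the plan.

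1. **Randomisation is concealed and 1:1.** A reader might infer that an omitted setting factor confounds the treatment contrast. It does not: the imbalance has expectation zero, and the type I error already allows for it. This stands.
2. **No stated aim asks for efficacy by pathway.** A reader might infer from the Background that the trial undertakes to answer that question. The sentence there is a statement of evidence need, and the Discussion presents the two-unit collaboration as a way to widen the severity range. This also stands. However, the article does make identifying who benefits a leading purpose, and objective 3 is where that is analysed.
3. **Severity already captures part of pathway.** NIHSS and MoCA are strata, and severity and baseline function are covariates. This stands in part. The Background says only that severe and mild patients usually or frequently follow the two routes, so severity does not determine them.
4. **The article is condensed.** Its covariate list need not be exhaustive, and an analysis plan that is not shown may add terms. So it cannot be said that the question will go unanswered. Still, the article does name both the primary test and a specific covariate list, and unit is in neither.

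Pooling varied usual care is a legitimate pragmatic choice and is not criticised here. The suggested remedy also has a limit: a patient enrolled at the stroke unit may go to any of the three recorded destinations, so unit does not identify pathway.

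**Conclusion.** The point holds as a modest, inexpensive improvement to the analysis, not as a flaw in the validity of the randomised comparison. A likely prognostic factor, fixed before randomisation, is left out of the strata, the between-group comparisons and the listed moderators. Chance imbalance in it has an SD of about 9 points before any help from NIHSS stratification, and typically moves the risk difference by 2 to 4 points. Adjustment would remove about 3% to 12% of outcome variance. These sizes rest on the assumed 25% share, the assumed 20 to 40 point risk gap and an overall risk near 50%. They are upper figures to the extent that severity strata already balance the units. Any analysis of effect by unit would be exploratory, with interaction power of about 25% to 31% even for a large contrast.

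**What to change.** Leave the ongoing randomisation unchanged and change the analysis wording before outcomes are analysed:

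- **Objectives 1 and 2:** adjust the between-group comparisons for enrolling unit. For the primary outcome, use for example a Mantel-Haenszel (stratified) or standardised risk difference.
- **Objective 3:** add enrolling unit as a prespecified exploratory effect modifier, and show the primary outcome by arm within each unit.
- **Caveats to state:** power for this interaction is low, and enrolling unit is only a proxy for care pathway.
- **Discharge destination:** report it descriptively, unless it is shown to be fixed before randomisation. The article does not give the order of the two events.

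The cost is one more model term and imprecise within-unit estimates, with about 25 patients in the smaller unit under the assumed share. Table 1 does not list enrolling unit as a data item, so the sponsor should confirm that it is recorded for every patient. The trial should know it from recruitment.

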**Figure 2 F2:**
[figure not shown]
Flow-chart of the CIPS-TER study.

## Discussion

Post-stroke cognitive impairment is a very common complication. Available epidemiological data report that about 75% of stroke patients experience cognitive worsening in the acute phase, which for many patients may persist in the medium to long term. These early forms of cognitive impairment could benefit from specific treatments (Ye et al., 2022). In this setting, a randomized controlled clinical trial to evaluate the effectiveness of telerehabilitation could expand knowledge and might bring evidence on feasibility in the acute stroke setting, cost-effectiveness, usability of delivery technologies, and, most importantly, help in the identification of the ideal type of patient who may benefit from such treatment. CIPSTER has been designed with these purposes.

Cognitive rehabilitation interventions focus on restorative and compensatory strategies that aim to restore cognitive function through repeated practice, develop new behaviors to compensate for cognitive deficits, and adapt to these cognitive deficits by reducing the effects of cognitive impairment on functional ability using strategies that minimize demands on attention skills. Post-stroke cognitive rehabilitation interventions have shown some benefits, but evidence is generally limited. Evidence from Cochrane showed that the effectiveness of cognitive rehabilitation for cognitive deficits following stroke remains to be confirmed (Chung et al., 2013; Loetscher et al., 2019; das Nair et al., 2016). Cognitive rehabilitation may improve some specific aspects of attention or executive functions immediately after treatment, but there is no evidence on the persistence of benefits. Improvements after cognitive rehabilitation are often limited, short-term, and dependent on various factors, such as severity of injury, timing of intervention, and type of treatment approach. It is also important to emphasize that tailoring interventions to patients' individual needs is critical to achieve more effective outcomes.

In 2014, Cicerone et al. published recommendations based on preliminary evidence to provide cognitive rehabilitation after stroke for attention deficits, neglect after right-hemisphere stroke, mild memory deficit (compensatory strategies), language deficits after left-hemisphere stroke, deficits in executive functioning, and comprehensive-holistic neuropsychological rehabilitation to reduce cognitive and functional disability after stroke (Cicerone et al., 2019). Telerehabilitation could be a possible alternative to in-person therapy for stroke patients, offering a reasonable model for service delivery, particularly in resource-limited settings (Maresca et al., 2020; Torrisi et al., 2019; Sarfo et al., 2018). The first issue in this regard would be to compare the efficacy between telerehabilitation and traditional “pen-and-paper” rehabilitation. So far, available evidence suggests that the efficacy might be comparable (Ye et al., 2022). Recently, cognitive telerehabilitation has received attention, although, as reported in the Cochrane review by Laver et al. (2020), further investigations are needed as the available evidence suffers from major methodological concerns, mainly small sample size and variability in assessment and treatment options (Laver et al., 2020). There is also growing interest in the use of computerized tools for post-stroke cognitive rehabilitation, which could be very useful in clinical practice for the treatment of specific deficits, potentially enhancing the personalization of interventions (Borsotti et al., 2020). Table 3 shows an overview of main randomized and non-randomized clinical trials on cognitive telerehabilitation in recent years (Nikolaev and Nikolaev, 2022). A notable observation is the consistently small sample size across all studies. In this regard, we propose to randomize a higher number of patients compared to previous studies (Withiel et al., 2019; Gil-Pagés et al., 2018; Faria et al., 2020; Lawson et al., 2020; Isernia et al., 2019; Maresca et al., 2019). CIPSTER is a real-world setting RCT study in the field aspiring to randomize 100 acute stroke patients. However, the relatively modest sample size may still represent a limitation, potentially reducing the statistical power and limiting the generalizability of the findings.

**Table 3 T3:** Overview of main randomized and non-randomized clinical trials on cognitive telerehabilitation in recent years.

**References**	**Type of study**	**Participants**	**Time since stroke**	**Type of cognitive telerehabilitation**	**Duration**	**Intensity**
Withiel et al. (2019)	RCT	65 Memory skills group (MSG, *n* = 24); computerized cognitive training (CCT, *n* = 22); waitlist control participants (WC, *n* = 19)	Chronic	Memory skills group vs. cognitive games online	6 weeks	MSG: 120 min/day 1 times a week CCT: 30 min/day 5 times a week
Gil-Pagés et al. (2018)	RCT	40 Experimental intervention (GNPT^®^, *n* = 20) or sham intervention (ictus.online, *n* = 20)	Chronic	Computerized cognitive telerehabilitation (attention, memory and executive functions exercises) vs. video with quiz	6 weeks	GNTP^®^: 1 h/day 5 times a week Ictus.online: 4 videos of 10 min 5 times a week
Faria et al. (2020)	RCT	32 Reh@City v2.0 (adaptive cognitive training through everyday tasks VR simulations, *n* = 17) vs. Task generator (TG: content equivalent and adaptive paper-and-pencil, *n* = 19)	Chronic	Virtual reality vs. Internet cognitive tasks	4 weeks	12 supervised sessions 3 times a week
Torrisi et al. (2019)	CT	40 Experimental group (*n* = 20) vs. Control group (*n* = 24, standard cognitive training)	Chronic	VR-Evo and VRRS Home Tablet	12 + 12 weeks	VR-Evo 50 min sessions 5 times a week + VRRS Home Tablet 50 min sessions 3 times a week
Lawson et al. (2020)	CT	46 Telehealth delivery condition (*n* = 28) vs. Face-to-face condition (*n* = 18)	Subacute	Zoom videoconferencing	6 weeks	2 h session 1 time a week
Isernia et al. (2019)	CT	45 HEAD rehabilitation in clinic (ClinicHEAD, *n* = 45) + Telerehabilitation at home (HomeHEAD, *n* = 15).	Chronic	Cognitive TeleRehabilitation	4 + 12 weeks	ClinicHEAD: 45 min/day, 3 times a week HomeHEAD: 30–45 min/day 5 times a week
Maresca et al. (2019)	CT	30 Experimental group (*n* = 15) vs. Control group (*n* = 15, paper-pencil tools)	Chronic	Virtual Reality Rehabilitation System-Evo and virtual reality rehabilitation system Home Tablet	24 weeks	50 min/day 5 times a week

RCT, randomized clinical trials; CT, Clinical trials (non-randomized clinical trials).

Another limitation concerns the inclusion and exclusion criteria: usually, in stroke cases, severe strokes and patients with aphasia are excluded, which obviously limits the generalizability of the results. Based on the inclusion and exclusion criteria, we will be able to assess patients with severe cognitive deficits, including mild aphasia, as well as those with very mild deficits, embracing the whole spectrum of post stroke cognitive deficits. By means of the collaboration between a University Hospital Stroke Unit and a Neurorehabilitation ward in rehabilitation Hospital we aspire to test cognitive telerehabilitation in a wide spectrum of stroke severity, in both ischemic and haemorrhagic strokes. This approach will enable the inclusion of patients with a broad spectrum of post-stroke deficits.

A further limitation relates to the risk of non-adherence to treatment. The intensity of the intervention protocol (daily 1-h sessions for 8 weeks) may pose challenges to patient compliance and increase the likelihood of dropout. For this reason, the CIPSTER trial is designed as a feasibility study.

In addition, it is important to acknowledge that the observed improvements in cognitive functions at six-month follow-up might partially reflect the natural course of post-stroke recovery, which tends to be more pronounced in the first few months. Therefore, attributing all the cognitive gains only to the intervention may be confounded by this spontaneous recovery process. The longitudinal evaluation will allow this to be clarified. In fact, the study outcomes will be defined according to standardized criteria based on an extensive neuropsychological and functional evaluation. To limit dropout rates, we also plan to include those patients who will not be able to attend the final visit in person, allowing an extensive phone interview. Of course, at the end, we will compare possible differences between groups.

Last but not least, CIPSTER will shed light on the feasibility of managing cognitive problems also in a very acute phase after stroke, within 3 weeks from stroke onset. Compared with the available evidence, only few studies examined cognitive outcome in this acute phase (Zucchella et al., 2014; Prokopenko et al., 2013), with most focusing on the chronic phase (Ye et al., 2022).

The results of CIPS-TER study may thus contribute to the knowledge on the effects of an early cognitive telerehabilitation on the reduction of persistent cognitive and functional burden in stroke patients, and thus on the potential benefits of including cognitive telerehabilitation as an effective component of post-stroke care pathways after discharge from inpatient care. In line with precision medicine, CIPS-TER project could also help to highlight which clinical features characterize stroke patients who could maximally benefit of such cognitive interventions. Finally, experiences and setups gathered within CIPS-TER project could represent a technical and methodological background for future studies aimed at the development and/or the evaluation of cognitive telerehabilitation systems in stroke patients.

